There have only been a few trials to address the specific needs of colorectal cancer survivors, including one RCT of a psychosocial intervention [21] and one RCT of a lifestyle intervention [18]. These studies have demonstrated effectiveness although both identified a number of limitations. The psychosocial trial included n = 249 survivors and the intervention group (n = 125) received 10 home-visits over two years from health professionals. The intervention group had significantly lower occurrence of symptoms of fatigue at three months follow-up, however there were no intervention effects at two years. This study was limited by differential compliance with the follow-up interviews, and the control group received some psychosocial intervention due to inexperienced staff. Furthermore, the content of the home visits was not theory-driven or structured as the topics discussed were set by the participants [21]. The lifestyle trial [18] included 102 survivors and the intervention group (n = 69) completed a home-based, personalised exercise program for 20–30 minutes three to five times per week. Intention-to-treat analyses revealed no differences in quality of life between the intervention and control groups, although exploratory analyses found that intervention participants who increased their physical fitness reported higher levels of quality of life and lower levels of anxiety and depression. Investigators reported exercise contamination in the control group as the study team contacted both the intervention and control participants weekly to report their exercise levels.

Previous research has suggested that interventions to improve quality of life after colorectal cancer may be most effective if they target symptom management, psychosocial and lifestyle variables, or health behaviours, in a comprehensive and integrated approach [22]. Further, patients have expressed the need for support with symptom management, psychosocial and lifestyle factors following a diagnosis of colorectal cancer [23]. However, despite the importance of comprehensive support and the promising results of previous interventions, to our knowledge there has been no previous trial of a broad and integrated supportive care program for colorectal cancer survivors. Accordingly, we have designed an intervention that focuses on symptom management, psychosocial and lifestyle support for recently diagnosed colorectal cancer survivors.

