Based on our past experience of recruiting colorectal cancer patients with this method, we anticipate approximately 80% of doctors will give permission for patients to be contacted and approximately 60% of patients will consent to participate. We therefore anticipate a final sample size of approximately n = 350 eligible participants (n = 175 in the intervention and control conditions at Time 1). Conservatively allowing for 20% attrition during the intervention, we expect n = 140 subjects per condition at Time 2. Sample size analysis indicated that 130 subjects per condition (intervention and control) or a total of 260 were required to detect, with 80% power and type I error of 5% (two-tailed), a moderate effect size in quality of life of 0.35.

Upon receipt of the completed consent package, all patients will be phoned by the project team to complete a brief screening instrument to assess factors that would exclude participation in the trial (physical activity using the Godin Leisure-Time Exercise Questionnaire [45], fruit and vegetable intake using brief questions developed by the Cancer Council NSW [46], and BMI elicited from self reported weight and height. Telephone interviewers will then complete the Time 1 interview, and computer-generated randomisation to study condition will occur following the completion of the Time 1 interview. Randomisation will be conducted by the project manager and concealed from investigators.

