### Study Integrity

The study design will be guided by the CONSORT statement [52], and randomisation to study condition will occur following the completion of Time 1 assessment. Project staff tracking data collection will be blinded to study condition. Randomisation will occur using block randomisation undertaken by the study manager and concealed from investigators. The intervention protocol will be manualised, and all intervention calls will be audio-taped with a proportion reviewed to ensure adherence to the delivery of the intervention protocol. All analyses will be conducted on the basis of intention to treat.

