### Data Analyses

Each hypothesis will be tested independently, taking into account hypothesised predictors as well as potential confounding factors (e.g. age, gender). Multiple (linear, multinomial or logistic) regression models will be fitted to consider the relative strength of cross-sectional associations between primary outcome variables (continuous, categorical or dichotomous) and patient characteristics. Repeated-measures regression models will be used to analyse and summarise changes in primary outcome variables over time and to determine the relationships with the various demographic, clinical, lifestyle, and psychosocial characteristics over the three measured time points. The effect of the intervention will be assessed by including a dichotomous variable (control/intervention) in the model, and assessing its interaction with the time-dependent response variable. Repeated-measures regression models will use a generalised estimating equations approach to account for the expected missing data due to attrition over time. Variables measuring health outcomes at Time 1 will be included in subsequent models to control for their effect on health outcomes in later time periods. Exploratory analyses on effect modification and mediation will also be conducted. Effect modification will be assessed through subgroup analyses and the introduction of interaction terms into the models to detect statistical differences between stratum-specific estimates. Standard statistical software including STATA (STATA SE 10.0; StataCorp, College Station, TX), and SPSS (version 14.0 for Windows) will be used for analysis and data management.

For the cost effectiveness analyses, incremental cost-effectiveness rations combining cost and health outcome data will be calculated. The incremental difference in costs between the 2 groups will be divided by the difference in QALY's (and other secondary health benefits) between the groups at Time 2 to generate the incremental cost-effectiveness ratio. This represents the additional cost and health effects of the intervention above the control condition. One-way sensitivity analyses will be undertaken to test the robustness of the ratios to variation in key parameters. Detailed probabilistic (multivariate) sensitivity analysis will be undertaken for all projections and parameters with uncertainty and/or variability using TreeAge Pro 2009 (Healthcare module) software (TreeAge Software Inc, Williamstown, MA, USA).

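### GEE is said to account for attrition, but unweighted GEE does not do so by itself; the exposure is mainly the Time 3 effect, if dropout depends on the Time 2 outcome differently by arm

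*Protocol article*

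**What the plan says.** Under Data Analyses, the protocol article fixes both the method and the reason for it: "Repeated-measures regression models will use a generalised estimating equations approach to account for the expected missing data due to attrition over time". It mentions no weighting or imputation and no assumption about why data are missing. The only sensitivity analyses in that section concern the cost-effectiveness ratios.

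The same section adds baseline adjustment: "Variables measuring health outcomes at Time 1 will be included in subsequent models". On the treatment effect it says: "The effect of the intervention will be assessed by including a dichotomous variable (control/intervention) in the model", with an interaction over time. Primary outcomes may be continuous, categorical or dichotomous.

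On the amount of loss, Sample Recruitment Procedures says: "Conservatively allowing for 20% attrition during the intervention, we expect n = 140 subjects per condition at Time 2". No loss is given for Time 3, although the Study Aims name both Time 2 and Time 3 for the primary outcomes. Study Integrity says: "All analyses will be conducted on the basis of intention to treat".

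**The concern.** The sentence credits GEE with a property that it does not have in general. Solving the unweighted estimating equations on observed visits tolerates unequal numbers of visits. It does not restore the mean that would have been seen had nobody left, unless dropout is unrelated to the outcomes given the covariates in the mean model. This is a point about what the document asserts, not about detail that an analysis plan might supply.

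The mechanism is plausible here. Fatigue, quality of life and activity could each influence whether someone stays. The arms also differ in burden: up to 11 coaching calls against brochures and a newsletter. The Background criticises an earlier colorectal trial on related grounds: "This study was limited by differential compliance with the follow-up interviews". If coached participants who do poorly at Time 2 leave more often than comparable controls, the Time 3 comparison favours the intervention.

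**Working it through.** **The plan's own figures.** For 0.35 SD, 80% power and two-sided 5%, the two-sample t-test needs 129.1 per arm, so 130 as stated. Loss by Time 2: 175 × 0.80 = 140 per arm, as stated. These reproduce and are not in question.

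**Time 2.** The only earlier outcome is Time 1. If it is in the mean model, dropout that depends on it leaves a correctly specified GEE unbiased.

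**Time 3.** Dropout after Time 2 can depend on the Time 2 score, which is not a covariate. With equal correlation ρ between visits, the coefficient of the Time 2 outcome in the regression of Time 3 on Times 1 and 2 is ρ/(1+ρ): 0.33 at ρ = 0.5, 0.375 at 0.6, 0.41 at 0.7. Let δ be the shift in the Time 2 score, given Time 1, among those who stay. Then approximately

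bias at Time 3 (independence GEE) ≈ ρ/(1+ρ) × (δ intervention − δ control).

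So the bias depends on the difference between arms. Equal shifts cancel.

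**Simulation A** (assumptions, not from the documents, except the 20% loss and the 0.35 SD effect): normal outcomes, ρ = 0.5 and 0.7, Time 1 as covariate, 20% lost at random by Time 2, then logit P(drop) = −1.6 + slope × Time 2 score. Slopes (intervention, control) were (−1, 0), (−1, 0.5) and (−1.5, 0). The further loss is 16.5–17.2% of those seen at Time 2. Total loss by Time 3 is then 0.20 + 0.80 × 0.165 = 33.2% up to 0.20 + 0.80 × 0.172 = 33.8%.

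| Estimator, Time 3, truth 0.35 | Estimate |
|---|---|
| Independence GEE | 0.378–0.406 |
| Exchangeable GEE | 0.350–0.354 |
| Likelihood-type, using the Time 2 score | 0.346–0.353 |
| Independence GEE, equal slopes (−1, −1) | 0.336–0.344 |
| Independence GEE, mild slopes (−0.3, 0) | about 0.36 |

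The first row is a bias of 0.378 − 0.35 = 0.028 to 0.406 − 0.35 = 0.056 SD, or 8% to 16% of 0.35. With equal slopes the bias is −0.014 to −0.006, slightly towards no effect.

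**Simulation B** (separate assumptions: ρ = 0.6, 20% loss at Time 2 and about 30% by Time 3, log-odds of dropout changing by 1 per SD, 200,000 subjects, Monte Carlo error about 0.005). Bias with Time 1 as covariate:

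| Dropout | Time 2, all models | Time 3, independence | Time 3, exchangeable or unstructured GEE | Time 3, likelihood |
|---|---|---|---|---|
| Completely at random | +0.005 | +0.001 | +0.001 | +0.001 |
| Prior outcome, same in both arms | +0.008 | +0.002 | +0.002 | +0.002 |
| Prior outcome, intervention arm only | +0.003 | +0.034 | +0.007 | +0.006 |
| Prior outcome, opposite by arm | 0.000 | +0.062 | +0.008 | +0.006 |
| Current unseen outcome, intervention arm only | +0.119 | +0.107 | +0.099 | +0.099 |

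The two simulations agree: +0.03 to +0.06 SD at Time 3 for independence GEE under arm-specific dropout, and almost nothing at Time 2 unless dropout depends on the unseen value.

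**The case against.** The strongest objection is that the protocol never names a working correlation. On the same simulated data an exchangeable GEE with Time 1 as covariate is essentially unbiased, so the inflation belongs to the independence structure and not to every GEE. This stands, and it limits the size of the point. It does not rescue the sentence. The near-robustness comes from modelling the correlation well for a continuous outcome. It was checked only for normal data, while the plan also allows categorical and dichotomous primary outcomes.

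It is also fair that the bias needs strong dropout differing by arm and a Time 3 loss that the documents do not give. The differential compliance in the Background belongs to another trial, and retention measures are planned here. The choice of working correlation and a delta-type sensitivity analysis are matters commonly left to an analysis plan, so their absence is not the complaint.

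Three stronger readings are tempting but not supported:

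- A reader might infer that the analysis is valid only if dropout is completely at random. The planned Time 1 covariates allow dropout to depend on them.
- A reader might infer that the stated 20% loss biases the primary effects generally. That figure applies by Time 2, where dropout driven by Time 1 gives about zero bias.
- A reader might take the wording "psychosocial characteristics over the three measured time points" to mean that Time 1 is a response. Independence GEE then gave +0.11 to +0.21 SD at Time 2 and +0.17 to +0.33 at Time 3 in Simulation B. But the section also puts Time 1 outcomes into later models as covariates, so these figures cannot be taken as what the plan implies.

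Nor does the intention-to-treat statement depend on GEE: it is a separate principle about analysing participants as randomised.

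**Conclusion.** The concern holds in limited form. The stated rationale is wrong: choosing GEE does not by itself account for attrition. With Time 1 as covariate, the practical exposure is mainly the Time 3 effect when leaving depends on the Time 2 outcome differently by arm. The size is about 0.03 to 0.06 SD on a true 0.35 SD. It rests on independence GEE, about 17% further loss among Time 2 completers, and log-odds slopes of −1 to −1.5 per SD in the intervention arm against 0 to 0.5 in the control arm (Simulation A); Simulation B gives the same range with a smaller loss. With equal slopes, or a near-correct working correlation for a continuous outcome, it is about 0.01 SD or less. None of the dropout mechanisms comes from the documents, so these figures show what is possible and do not predict the trial's bias. The sample size is unaffected.

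**What to change.** For the continuous primary outcomes, replace unweighted GEE with a likelihood-based mixed model for repeated measures, with unstructured covariance and Time 1 as covariate. This is valid under missing at random, because it uses the Time 2 score of those who leave afterwards. For categorical or dichotomous outcomes, or if GEE is kept, use inverse-probability-weighted GEE or multiple imputation, with the Time 2 outcome in the weighting or imputation model. In either case delete the claim that GEE alone accounts for attrition and state the missing-at-random assumption.

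A sensitivity analysis for data missing not at random is optional. None of these primary methods corrects that mechanism: in Simulation B the likelihood model was also biased, by about 0.10 to 0.12 SD.

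The cost is a change of wording, a little more programming, and open reliance on missing at random. No extra data or participants are needed.

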## Methods/Design

### Study Design

The study is a two-armed prospective RCT in which approximately 350 colorectal cancer survivors will be randomised in a 1:1 ratio to the intervention or control group using a computer-generated random numbers sequence. Participants in both groups will complete assessments at baseline (Time 1), post-intervention or 6 months follow-up (Time 2), and at 12 months follow-up for longer term effects (Time 3).

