#### Intervention

The intervention will include (i) telephone delivered health coaching sessions; (ii) participant handbook, (iii) regular motivational postcard prompts; (iv) pedometer; (v) and the quarterly study newsletter sent to control participants. The intervention will be detailed in an intervention manual including health coaching session scripts and worksheets. The intervention will focus on symptom management, as well as psychosocial and lifestyle support to help participants manage the current and possible future stresses associated with colorectal cancer and make positive lifestyle changes. The intervention framework is based on ACT as outlined previously [24,26] and limited session content has been drawn from a current trial of a psychosocial and physical activity intervention to improve heart health [47].

The sessions will include: the cancer experience; colorectal cancer-related symptoms; specific ACT components in relation to lifestyle behaviours (values, mindfulness, defusion or mindfulness of thoughts, acceptance or mindfulness of feelings, and committed action); and strategies to enhance improvement in lifestyle behaviours consistent with the national recommendations and individual goals [42-44,48-51]. Intervention strategies will be consistent with the session content including: ACT-strategies; motivational interviewing; problem solving; action planning and goal setting; as well as reviewing and ongoing monitoring.

The health coaching sessions will be delivered by study-trained health coaches who will be guided by a custom developed web-based computer application and will key enter all session information. Health coaches will receive comprehensive training in: colorectal cancer incidence, treatment, symptoms and outcomes; ACT, behavioural models of health and illness and behaviour change; as well as national guidelines for lifestyle behaviours [42-44,48-51]. Role-play and simulated calls will be conducted to prepare health coaches for program delivery. The first 10 sessions will be delivered bi-weekly over a five month period, followed by the final telephone session four weeks later to promote self management techniques and long term maintenance of lifestyle improvements.

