###### Quality of life

We will use the Short Form-36 (SF-36), a widely used measure that has published norms for the Australian general population[55,56]. The SF-36 contains a mental health and physical health summary scale suitable to measure the impact of the intervention on patients' wellbeing, and generates a preference-based utility instrument SF-6D which will be used in the cost-effectiveness analyses.

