#### Cost Effectiveness

In order to assess the economic value of the intervention, several health outcome variables (detailed above) will be combined with resource data to produce cost-effectiveness ratios at Time 2. Taking a 'health system' perspective, the types of resources in the analyses will include all intervention resources recorded by the study manager (e.g. health coach materials), participant health care utilisation (e.g. hospital admissions), community health resources and medications. Detailed data will be collected by self report and validated with a randomised sub-sample of 20% of patient records and provider surveys. Resources will be valued using nationally applicable sources (e.g. Diagnosis-Related Group codes for hospital admissions and Pharmaceutical Benefits Scheme cost codes for medications). All costs will be aggregated for the control and intervention arms. The primary health benefit for the cost effectiveness analyses will be quality-adjusted life years (QALYs). Quality of life will be measured by the SF-36; the SF6D algorithm will be used to produce QALY-weights on a 0–1 scale. Secondary health benefits will include the mean change in lifestyle factors and health outcomes.

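### The cost-effectiveness ratio stops at 6 months, so it carries essentially all the coaching cost but leaves out months 6 to 12, for which utility data are due at Time 3

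*Protocol article*

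**What the plan says.** Two sections of the protocol article fix the horizon, and they agree. Under Cost Effectiveness, health outcomes "will be combined with resource data to produce cost-effectiveness ratios at Time 2". Under Data Analyses, the difference in costs is "divided by the difference in QALY's (and other secondary health benefits) between the groups at Time 2 to generate the incremental cost-effectiveness ratio". No ratio at 12 months is planned.

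On costs, Cost Effectiveness states that "the types of resources in the analyses will include all intervention resources recorded by the study manager", together with participants' health care use, community health resources and medications. On timing, the Intervention section says: "The first 10 sessions will be delivered bi-weekly over a five month period, followed by the final telephone session four weeks later". That last call is meant to support self-management and long-term maintenance.

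Follow-up goes further than the ratio does. Study Design has both groups assessed "at 12 months follow-up for longer term effects (Time 3"). Study Aims lists quality of life among the primary outcomes at both Time 2 and Time 3, and Measurement says that most data are collected at all three times. The SF-36 "generates a preference-based utility instrument SF-6D which will be used in the cost-effectiveness analyses".

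**The concern.** Cost-effectiveness is one of the trial's two aims and one of its stated hypotheses. The Discussion expects the programme to be ready for practice, so the ratio may inform a funding decision.

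The programme spends its money early and is designed to have effects that last. A cut at 6 months charges the intervention arm with essentially all its coaching cost and credits it only with the QALYs gained while coaching was under way. Whatever happens to utility or health care costs in the next 6 months, good or bad, does not enter the ratio. The 12-month utilities are due to be collected anyway, so the plan sets aside information that it will have.

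**Working it through.** The plan gives no cost, utility or ratio, so it has no figure of its own to reproduce on this point. The sample size (130 per condition for a quality-of-life effect of 0.35) is not affected. The check is symbolic, and its multipliers do not depend on the size of the utility gain.

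**Inputs from the protocol article**
- Assessments at 0, 6 and 12 months (Study Design).
- Ratio taken at Time 2, that is 6 months or 0.5 year (Cost Effectiveness; Data Analyses).
- Eleven sessions: ten over five months and one four weeks later, so all within about 6 months (Intervention).
- SF-6D weights on a 0 to 1 scale, derived from the SF-36 (Cost Effectiveness; Quality of life).

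**Assumptions, not in the document**
- Equal utility in the two arms at Time 1.
- A positive utility difference D at Time 2, reached linearly.
- A share r of D remaining at Time 3, with linear change in between.
- A positive incremental cost C to Time 2, and a further incremental cost X in months 6 to 12.

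**QALY gain (trapezoid areas)**
- To Time 2: 0.5 × (0 + D)/2 = D/4.
- Months 6 to 12: 0.5 × (D + rD)/2 = D(1 + r)/4.
- To Time 3: D/4 + D(1 + r)/4 = D(2 + r)/4.

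The 12-month gain is therefore (2 + r) times the 6-month gain. With X = 0, the Time 2 ratio is (2 + r) times the 12-month ratio.

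| Share kept at Time 3 (r) | Gain to Time 2 | Gain to Time 3 | Time 2 ratio ÷ 12-month ratio, X = 0 |
|---|---|---|---|
| 0 (gone) | D/4 | D/2 | 2.0 |
| 0.5 | D/4 | 5D/8 | 2.5 |
| 1 (maintained) | D/4 | 3D/4 | 3.0 |

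As an illustration with an assumed D of 0.03, the gain is 0.0075 QALY to Time 2, against 0.0150 (r = 0) to 0.0225 (r = 1) to Time 3.

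**Effect of later costs**
- Time 2 ratio: C ÷ (D/4) = 4C/D.
- 12-month ratio: (C + X) ÷ (D(2 + r)/4) = 4(C + X)/(D(2 + r)).
- The two are equal when (C + X)/(2 + r) = C, that is X = (1 + r)C.

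The break-even extra cost is thus C at r = 0, 1.5C at r = 0.5 and 2C at r = 1. Below it the 12-month ratio is lower than the Time 2 ratio; above it, higher. If the intervention saves health care costs after month 6 (X negative), the 12-month ratio falls further.

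**The case against.** The two sections agree on Time 2. The aim that names both Time 2 and Time 3 is the effectiveness aim; the cost-effectiveness aim names no time point. There is therefore no contradiction, and a ratio over the intervention period is limited but interpretable. This stands: the point concerns a choice of horizon.

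A 12-month ratio needs costs as well as utilities, and the article does not say that resource use is collected at Time 3. The only attrition allowance is the 20% to Time 2. This also stands, and it makes the fix somewhat more expensive.

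Data Analyses mentions sensitivity analysis of projections in decision-modelling software, which might mean modelling beyond Time 2. It names no model, no horizon and no use of Time 3 data, and the ratio as defined stays at 6 months. This does not remove the point.

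A reader might also infer more than the document supports:
- *That the denominator is the bare utility difference at 6 months.* This would overstate the QALY gain 4-fold (D ÷ D/4). But Cost Effectiveness separates QALY weights from QALYs, so the natural reading is QALYs accrued to Time 2. The error is not shown.
- *That the ratio is bound to be biased against the intervention.* The direction depends on costs in months 6 to 12, which are unknown.
- *That area-under-the-curve and baseline-utility methods are missing.* An article commonly leaves these to the full protocol or analysis plan, so their absence is no finding.

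**Conclusion.** The point holds as a comment on the horizon. The plan limits its only incremental ratio to 6 months, counts essentially all the coaching cost in it, and makes no use of the 12-month utilities. Nothing in the article justifies stopping there.

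Under a positive gain that builds linearly, equal baselines and no cost difference after month 6, the 6-month cut captures one third (gain maintained) to one half (gain gone by Time 3) of the QALYs gained over 12 months. The Time 2 ratio is then 3 to 2 times the 12-month ratio. These multipliers are illustrations under stated assumptions and do not predict the trial's result. Costs in months 6 to 12 could shrink, reverse or enlarge the gap.

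The effectiveness comparisons and the sample size are untouched. The costing perspective, described as cost to government in the Abstract and as health system under Cost Effectiveness, is a separate minor wording point that adds no weight here.

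**What to change.** In Cost Effectiveness and Data Analyses, add a within-trial 12-month incremental cost-effectiveness ratio:
- QALYs accrued over Times 1, 2 and 3 from the SF-6D, with the difference between arms adjusted for Time 1 SF-6D;
- costs accumulated over the same 12 months;
- results reported alongside the 6-month ratio, preferably with 12 months as the base case. If 6 months is kept as the base case, give the reason.

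Ask the resource-use questions at the existing Time 3 interview if this is not already planned. This should be settled before those interviews begin, because costs not collected then may be hard to recover.

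The price is a few more interview minutes, more costing work (including any extension of the 20% validation against records) and more missing cost data at 12 months than at 6. No extra visit is needed, and neither the sample size nor the primary analyses change.

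### The ICER's QALY difference names no adjustment for Time 1 SF-6D, so taken as written it is unbiased but less precise than the collected data allow

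*Protocol article*

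**What the plan says.** Cost-effectiveness is the second of the two study aims and a stated hypothesis. Under Cost Effectiveness, QALYs are the primary health benefit, and resource data and outcomes are to be "combined with resource data to produce cost-effectiveness ratios at Time 2", that is, over six months. Utilities come from the SF-36: "the SF6D algorithm will be used to produce QALY-weights on a 0–1 scale". On costs, the section says: "All costs will be aggregated for the control and intervention arms".

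Under Data Analyses, the cost difference is to be divided by the QALY difference, and by the differences in the secondary benefits, "between the groups at Time 2 to generate the incremental cost-effectiveness ratio". One-way and probabilistic sensitivity analyses follow. No covariate or model is named for the QALY difference.

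The paragraph just before, on the repeated-measures regression models, is explicit about baseline: "Variables measuring health outcomes at Time 1 will be included in subsequent models to control for their effect on health outcomes in later time periods". It is written for the health-outcome models and is not carried over to the ICER. Under Study Design, both groups are assessed at baseline, six months and twelve months, so a Time 1 SF-6D value will be available.

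**The concern.** A six-month QALY built from Time 1 and Time 2 utilities contains the Time 1 value directly. That value precedes randomisation, so it carries no treatment effect and adds only noise to the arm comparison unless it is adjusted for. Even a QALY based on the Time 2 weight alone inherits some baseline imbalance through the correlation between the two measurements.

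An ICER is sensitive to this because it is a ratio with a small denominator. Over six months, a utility gain that emerges by Time 2 yields at most half that gain in QALYs, and a quarter of it under a two-point area under the curve. If the denominator is noisier than it need be, the ratio is less stable and the probabilistic analysis shows more uncertainty than the data require.

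**Working it through.** **The plan's own figures.** Under Sample Recruitment Procedures the article states 130 per condition for an effect size of 0.35, 80% power and two-tailed 5%. The normal approximation gives n = 2 × (1.960 + 0.842)² / 0.35² = 128.1, rounded up to 129. The t-based solution is 129.1, rounded up to 130, so the stated figure reproduces. With 20% attrition, 175 × 0.8 = 140 per arm at Time 2, which is used below.

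**Assumptions, none of them in the article.** SF-6D has the same SD, s, at Time 1 (U1) and Time 2 (U2). Their correlation r lies between 0.3 and 0.8. Three ways of forming the QALY are compared, because the article gives no rule.

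**Formulas (variance per participant, within arm).**
- Two-point area under the curve, 0.25 × (U1 + U2): unadjusted 0.0625 × 2(1 + r)s²; adjusted for U1, 0.0625 × (1 − r²)s². Ratio = 2/(1 − r).
- Time 2 weight only, 0.5 × U2: unadjusted 0.25 × s²; adjusted 0.25 × (1 − r²)s². Ratio = 1/(1 − r²).
- Change from Time 1, proportional to U2 − U1: unadjusted 2(1 − r)s²; adjusted (1 − r²)s², with the same scaling. Ratio = 2/(1 + r).

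**Unadjusted/adjusted variance ratio.**

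| r | Area under curve | Time 2 only | Change |
|---|---|---|---|
| 0.3 | 2.9 | 1.10 | 1.54 |
| 0.5 | 4.0 | 1.33 | 1.33 |
| 0.6 | 5.0 | 1.56 | 1.25 |
| 0.7 | 6.7 | 1.96 | 1.18 |
| 0.8 | 10.0 | 2.78 | 1.11 |

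Simulation of the area-under-the-curve case with 140 per arm gave ratios of 4.0 at r = 0.5 and 6.8 at r = 0.7. If the Time 2 SD is 0.8 to 1.25 times the Time 1 SD, that ratio at r = 0.5 runs from 5.1 down to 3.25.

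**What this means on the trial's own scale.** Suppose SF-6D at Time 2 moves by 0.35 s, borrowing the effect size that the article states for quality of life. No SD is then needed. Take r = 0.5 and 140 per arm:
- Area under the curve: true difference 0.25 × 0.35 = 0.0875 s. The unadjusted SE is √(0.0625 × 3 × 2/140) = 0.0518 s, so difference/SE = 1.69 and power at two-sided 5% is about 39%. The adjusted SE is √(0.0625 × 0.75 × 2/140) = 0.0259 s, so difference/SE = 3.38 and power is about 92%.
- Time 2 only: true difference 0.5 × 0.35 = 0.175 s. The unadjusted SE is 0.5 × √(2/140) = 0.0598 s, so difference/SE = 2.93 and power is about 83%.

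The article plans no test of the QALY difference; power serves here only as a yardstick.

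**Chance imbalance.** The SE of the Time 1 difference is √(2/140) = 0.120 s. A one-SE imbalance shifts the unadjusted area-under-the-curve difference, in expectation, by 0.25 × (1 + r) × 0.120 = 0.045 s at r = 0.5. That is about half of the 0.0875 s treatment difference above (0.045/0.0875 = 0.51).

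**The case against.** The strongest reply is that the ICER sentence is only the generic definition of the ratio. It does not call the difference raw, and how the difference is estimated is a detail that a protocol article often leaves to the full protocol or analysis plan. Data Analyses also opens by promising that each hypothesis will take potential confounders into account, and cost-effectiveness is one of the hypotheses. This has force: a reader who says that the plan specifies a raw difference is turning silence into a statement. What remains is that the article sets out the calculation as a two-group difference and confines its only Time 1 adjustment sentence to the regression models, so someone following the text would compute an unadjusted denominator.

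Other stronger readings also go beyond the text:
- A fixed four- to seven-fold loss of precision. It needs an area-under-the-curve QALY, equal SDs and r of about 0.5 to 0.7, none of which the article states. Under the other constructions the loss is much smaller.
- Bias. Randomisation keeps the unadjusted difference unbiased on average, so the issue is precision and chance imbalance.
- An ICER that cannot be interpreted at all. A wider interval does not establish that, and only an imbalance against the intervention could turn a true gain negative.
- Discarded patient-level pairing of costs and QALYs. Aggregating costs by arm may simply mean summing cost categories within arms, and the planned multivariate probabilistic analysis could preserve the correlation. The text supports neither this claim nor a demand for a bootstrap in its place.

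**Conclusion.** The point stands as an improvement available at almost no cost. As written, the ICER denominator carries no Time 1 SF-6D adjustment, and adding it gains precision under each of the three QALY constructions examined. The size depends mainly on the unstated construction: large for the area under the curve, modest for a Time 2 weight alone or for change. All the ratios rest on an assumed r and on roughly equal SDs. The three primary outcomes are not affected; the point concerns the second study aim only.

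**What to change.** State in the cost-effectiveness analysis that:
- each participant's six-month QALY is computed from the Time 1 and Time 2 SF-6D values;
- the between-group QALY difference is estimated by regressing the QALY on arm and Time 1 SF-6D;
- this adjusted difference forms the ICER denominator, and the estimate and its standard error supply the QALY input to the probabilistic sensitivity analysis already planned.

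If the full protocol or analysis plan already says this, a sentence in the cost-effectiveness text pointing to it is enough. The cost is a few lines of analysis wording and minor programming, with no new data collection and no change to the sample size.
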